### Statistical analysis

The primary analysis will be performed on the full analysis set (that is, all randomised participants for whom the primary endpoint (symptoms at 11 and 12 weeks) is available) using an analysis of covariance in the form of a general linear model incorporating terms for baseline frequency, treatment arm, centre, and other baseline characteristics which are thought a priori to strongly predict outcome.

Secondary and mechanistic endpoints were treated similarly, after transformation to approximate normality as required for continuous variables, while binary and count outcomes were handled by logistic or Poisson regression, as appropriate. All analyses were performed using the current version of STATA (StataCorp, Texas, USA), adopting the intention to treat principle following multiple imputation for missing data (with a sensitivity analysis for the missing at random assumption for the primary outcome). For mechanistic variables a per-protocol analysis was additionally performed.

No interim or subgroup analyses were planned for efficacy.

Assessment of safety followed the same principles as the assessment of efficacy except that the safety set (that is, all randomised participants who receive at least one dose of the study drug) were used.

Procedures for missing, unused and spurious data were handled by multiple imputation using the method of chained equations.

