### Sample size

Our previous study on diarrhoea-predominant IBS patients gives a mean stool frequency of 3.1 (standard deviation 2.0). Tuteja and colleagues reported mesalazine decreasing stool frequency by 1.4 bowel movements per day [14]. We calculated from these data that 108 completed patients (randomized 1:1 to mesalazine or placebo) would give the study an 80% power to detect such an effect at the 1% significance level (90% at 5% significance). As we had not accounted for attrition if participants withdrew, these participants were replaced in order to ensure 108 completed participants.

Much smaller numbers would be needed to assess the effect of mesalazine on mast cell numbers and tryptase release. Corinaldesi *et al*. reported a 36% decrease in mast cell numbers from mean 9.2 (standard deviation 2.5) [13], which would have required just 12 patients to show such a decrease with a power of 90% at the 1% significance level.

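### The primary analysis is defined in two incompatible ways, on participants with an available endpoint and as intention to treat after multiple imputation, so it is unsettled whether withdrawn patients count

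*Protocol article*

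**What the plan says.** All references are to the protocol article.

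- **Statistical analysis, first paragraph.** The primary analysis is an ANCOVA on what the article calls the full analysis set, defined as "all randomised participants for whom the primary endpoint (symptoms at 11 and 12 weeks) is available".
- **Statistical analysis, second paragraph.** All analyses are described as "adopting the intention to treat principle following multiple imputation for missing data", followed directly by "with a sensitivity analysis for the missing at random assumption for the primary outcome".
- **Statistical analysis, last paragraph.** "Procedures for missing, unused and spurious data were handled by multiple imputation using the method of chained equations".
- **Sample size.** The target of 108 is a number of completed patients. The article continues "As we had not accounted for attrition if participants withdrew", and then that "these participants were replaced in order to ensure 108 completed participants".
- **The interventions.** A participant who does not tolerate the current dose may reduce it or stop.

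The Abstract repeats the ANCOVA without naming an analysis set. No sentence says which rule is primary and which is supportive.

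**The concern.** If membership of the primary set requires an available week 11–12 endpoint, nobody in the set lacks that endpoint, and there is no missing primary outcome for the imputation to fill. If all analyses follow intention to treat after imputation, randomised patients without that endpoint belong in the primary comparison. The two rules give different analysed populations and so, in general, different estimates and p-values.

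Two things are at stake. First, having the endpoint is determined after randomisation. If withdrawal differs by arm and is related to stool frequency, the patients who remain are no longer a randomised comparison. Both routes are foreseeable here: stopping because the dose is not tolerated, and leaving because placebo does not help. Second, with two candidate primary results and no ranking, the choice could be made after the data are seen.

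**Working it through.** **1. The two rules side by side**

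| Randomised participant | Endpoint-available rule | Intention to treat with imputation |
|---|---|---|
| Week 11–12 diary present, on drug | in | in |
| Stopped drug, diary kept to week 12 | in | in |
| Withdrawn, no week 11–12 data | out | in, imputed |

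The rules differ only in the last row, which is also the group the Sample size section replaces.

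**2. The plan's own figure**

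The relevant figure is 108 completers (54 per arm). With a difference of 1.4, SD 2.0 and two-sided tests, the normal approximation gives 96 (80% power, 1% level) and 86 (90% power, 5% level). The t-based figures are 100 and 88. So 108 does not reproduce exactly and is on the conservative side: 54 per arm gives t-based power of 84.2% at 1% and 95.0% at 5%. That is a separate matter. Here 108 serves only as the completer target.

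**3. How many patients the choice affects**

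Randomised total = 108/(1 − d), rounded up. The dropout d is assumed, since the article gives none.

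| d | 108/(1 − d) | Randomised | Without endpoint |
|---|---|---|---|
| 5% | 113.7 | 114 | 6 |
| 10% | 120.0 | 120 | 12 |
| 15% | 127.1 | 128 | 20 |
| 20% | 135.0 | 135 | 27 |
| 30% | 154.3 | 155 | 47 |

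This treats everyone who does not complete as lacking the endpoint, so the last column is an upper figure if some keep the diary after stopping the drug.

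**4. Direction and size of the bias**

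In one arm, let c be the mean among those observed, d the dropout proportion, and g how many stools/day worse the dropouts would have scored. The mean over all randomised is (1 − d)c + d(c + g) = c + d·g, so the observed mean is too low by d·g. The mesalazine-minus-placebo difference is therefore shifted by

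−(d_mes × g_mes − d_plac × g_plac).

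A negative shift favours mesalazine. All inputs are assumed.

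| Dropout mes / plac | g, both arms | Shift (stools/day) |
|---|---|---|
| 20% / 10% | 1 | −0.10 |
| 20% / 10% | 2 | −0.20 |
| 25% / 10% | 1 | −0.15 |
| 25% / 10% | 2 | −0.30 |
| 15% / 15% | 1 or 2 | 0 |
| 10% / 20% | 1 | +0.10 |
| 10% / 25% | 2 | +0.30 |

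Against the 1.4 used for sample size, 0.10/1.4 = 7% and 0.30/1.4 = 21%. Equal dropout is not enough by itself. At 15% / 15% with g = 1 on mesalazine and 0 on placebo, the shift is −(0.15 × 1 − 0.15 × 0) = −0.15.

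**5. Does baseline adjustment remove it?**

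Trials with no treatment effect were simulated, 4,000 per setting, with about 108 completers and SD 2.0. The assumed correlation was 0.5 between baseline and final frequency, and 0.5 between final frequency and the tendency to drop out. ANCOVA on the observed cases gave:

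| Dropout mes / plac | Mean estimate | Type I error (nominal 5%) |
|---|---|---|
| 0 / 0 | 0.00 | 4.6% |
| 15% / 15% | 0.00 | 4.9% |
| 20% / 10% | −0.12 | 6.9% |
| 30% / 10% | −0.23 | 11.2% |

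Adjustment for baseline does not remove the shift. Swapping the arms reverses its sign.

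**The case against.** The strongest defence is that only one analysis carries the label primary, and that the imputation sentence can be read alongside it. The endpoint averages two weeks of diary, so a participant whose endpoint counts as available may still have missing days, and baseline covariates and secondary outcomes may be missing too. An available-case ANCOVA also relies on missingness being ignorable given its covariates, so a missing-at-random sensitivity analysis for the primary outcome does not by itself prove that this outcome is imputed. The article is also a condensation, and the imputation model may properly sit in the full protocol or the SAP.

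Part of this stands: what counts as available, and the details of the imputation model, are not findings here. The reconciliation still strains the text. The imputation sentence covers all analyses, and the sensitivity analysis is attached to it in the same breath. Even on that reading, randomised patients with no week 11–12 data stay outside the primary comparison, which does not fit the stated intention-to-treat principle. The article has not left the point out. It states two rules that disagree.

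A reader might infer more than the document supports:

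- **That the set is completers only.** It is defined by having the endpoint. Someone who stops the drug but keeps the diary is in it.
- **That replacement causes the bias.** It is a recruitment rule. It restores the number analysed but not the randomised comparison. Any bias comes from leaving out the withdrawn patients.
- **That the bias must favour mesalazine.** Excess withdrawal on placebo for lack of benefit would push it the other way.

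**Conclusion.** Wrong as written. The Statistical analysis section gives two incompatible definitions of the primary analysis, and they differ over randomised participants who withdraw without week 11–12 data. This rests on the text alone and holds even if the realised bias is nil.

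The size is conditional. With assumed dropout differing by 10 to 15 percentage points and dropouts 1 to 2 stools/day worse in both arms, the shift is about 0.1 to 0.3 stools/day, or 7% to 21% of 1.4. Its sign depends on which arm loses more patients, and it is zero if dropout is equal and alike in both. None of these dropout inputs is in the document, so the figures show what could happen and do not predict it.

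It might also be inferred that imputation settles the matter. It does not. Under missing at random it keeps every randomised patient and can use the earlier diary, but it does not remove bias from dropout that depends on the unobserved outcome.

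**What to change.** Name one primary analysis in the Statistical analysis section:

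- **Population.** All randomised participants, analysed as randomised, including those who withdrew and were replaced.
- **Missing outcome.** Missing week 11–12 stool frequency is multiply imputed by the chained equations already planned, using arm, site, baseline frequency and earlier diary data.
- **Supportive analyses.** The ANCOVA on participants with the endpoint available becomes a sensitivity analysis. The planned missing-at-random sensitivity analysis for the primary outcome is kept, because imputation alone does not deal with outcome-dependent dropout.
- **Sample size section.** Add one sentence that replacement concerns recruitment only and removes nobody from the primary analysis.

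The cost is a change of wording and a little more analysis work, since the imputation and the diary are already in the plan. The confidence interval may be slightly wider. That was not calculated, and informative earlier diary data could offset it.

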#### Secondary endpoint

Clinical secondary endpoints during weeks 11 and 12 of the treatment period:

1) Average daily severity of abdominal pain on a 0 to 10 scale.

2) Days with urgency.

3) Mean stool consistency using Bristol Stool Form Score.

4) Global satisfaction with control of IBS symptoms as assessed from the answer to the question ‘Have you had satisfactory relief of your IBS symptoms this week? Yes/No.’

Mechanistic secondary endpoints during weeks 11 and 12 of the treatment period:

1) Mast cell tryptase release during 6-hour biopsy incubation

2) IL-1β, TNF-α, histamine and serotonin secretion during same incubation

3) Small bowel tone assessed by volume of fasting small bowel water

4) Fecal tryptase activity

5) Difference in primary outcome measure between those with different TNFSF15 polymorphism

Ancillary secondary endpoints during weeks 11 and 12 of the treatment period:

1) EuroQol-5D (EQ-5D)

2) Centers for Disease Control and Prevention Health-Related Quality of Life (CDC HRQOL4)

3) Hospital, Anxiety and Depression Scale (HADS)

4) Patient Health Questionnaire-15 (PHQ-15)

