### Outcome measures

#### Daily symptom and stool diary

Participants completed a daily symptom and stool diary throughout their participation indicating hours of pain, severity of abdominal pain on a 0 to 10 scale, presence of urgency (yes/no) and bloating on a 0–10 scale. They were also asked on a weekly basis the following yes/no question: ‘Have you had satisfactory relief of your IBS symptoms this week?’

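### If days with urgency is analysed by Poisson regression with model-based standard errors, those errors will generally be wrong, in a direction not known in advance

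*Protocol article*

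**What the plan says.** Under Statistical analysis, the protocol article states that "Secondary and mechanistic endpoints were treated similarly" to the primary endpoint, whose model contains baseline, treatment arm, centre and other strong predictors. For non-continuous outcomes it adds that "binary and count outcomes were handled by logistic or Poisson regression, as appropriate". It provides for transforming continuous outcomes that are far from normal, but mentions no corresponding step for counts whose variance departs from the Poisson assumption. Missing data are to be handled by multiple imputation with chained equations.

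The Secondary endpoint section lists "Days with urgency" under the heading "Clinical secondary endpoints during weeks 11 and 12 of the treatment period". The Daily symptom and stool diary section shows the source item, "presence of urgency (yes/no", which is recorded each day. Each participant's value is therefore a whole number from 0 to 14.

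The article does not assign this endpoint to the Poisson model by name. It is the only clinical endpoint on the list that is naturally a count of days, so the assignment is the natural reading. No variance estimator is stated.

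**The concern.** Some patients will report urgency on almost every day and others on almost none, so the 14 daily answers from one person are correlated. That correlation pushes the variance of the sum up. The ceiling at 14 pulls it down, and more strongly the more common urgency is. A Poisson model with model-based standard errors allows for neither: it sets the variance equal to the mean.

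If clustering dominates, standard errors are too small and a chance difference between arms can be reported as an effect of mesalazine on urgency. If the ceiling dominates, standard errors are too large and a real effect can be missed. Urgency is one of the features by which the article's abstract characterises diarrhoea-predominant IBS, so either error would matter to readers.

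A lesser issue is that a count without a denominator treats 6 urgent days out of 8 recorded like 6 out of 14.

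**Working it through.** **Inputs.** The document gives no mean, standard deviation or correlation for urgency, so there is no stated figure to reproduce.

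- Maximum count: 14, from the two-week window.
- Arm size: 54, half of "108 completed patients (randomized 1:1 to mesalazine or placebo" in the Sample size section.
- Daily prevalence of urgency, p: not given; varied as a mean of 4, 7, 10 or 12 days out of 14.
- Within-person correlation of the daily answers, ρ: not given; varied from 0 to 0.5 below, and up to 0.6 in the adjusted simulation.

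**Step 1: variance against mean.** With a beta-binomial count out of 14, the mean is 14p and the variance is 14p(1−p)(1+13ρ). The ratio is

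φ = (1−p)(1+13ρ).

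Poisson assumes φ = 1, which holds only at ρ = p/[13(1−p)]. That is 0.03 at a mean of 4 days, 0.08 at 7, 0.19 at 10 and 0.46 at 12. Above that value the standard error is too small; below it, too large.

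**Step 2: true size of a nominal 5% test, no adjustment.** The model-based standard error is off by a factor of √φ, so

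size = 2[1 − Φ(1.96/√φ)].

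Example: mean 7 (p = 0.5), ρ = 0.2. φ = 0.5 × 3.6 = 1.8, √φ = 1.34, 1.96/1.34 = 1.46, size = 14.4%.

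| Mean days | ρ = 0 | ρ = 0.1 | ρ = 0.2 | ρ = 0.3 | ρ = 0.5 |
|---|---|---|---|---|---|
| 4 | 2.0% | 12.6% | 22.2% | 29.5% | 39.7% |
| 7 | 0.6% | 6.8% | 14.4% | 21.1% | 31.2% |
| 10 | <0.1% | 1.6% | 5.3% | 9.8% | 18.1% |
| 12 | <0.1% | 0.1% | 0.6% | 1.9% | 5.8% |

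The formula does not depend on arm size. Simulation with 54 per arm and no treatment effect agrees: 14 / 21 / 31% at a mean of 7 days and 5.4 / 9.8 / 18.1% at a mean of 10, for ρ = 0.2 / 0.3 / 0.5.

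**Step 3: baseline adjustment.** The planned model includes baseline, so the null simulation was repeated with a 14-day baseline count as covariate (1,000 trials per setting, latent correlation between baseline and outcome 0.3 or 0.6).

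| p | ρ | Model-based Poisson, correlation 0.3 / 0.6 |
|---|---|---|
| 0.5 | 0.2 | 13.2% / 10.4% |
| 0.5 | 0.4 | 23.7% / 19.4% |
| 0.5 | 0.6 | 31.4% / 26.5% |
| 0.7 | 0.2 | 4.6% / 4.2% |
| 0.7 | 0.4 | 13.8% / 10.0% |
| 0.7 | 0.6 | 20.3% / 17.9% |

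Monte Carlo error is about 0.7 percentage points at a true 5%. At p = 0.85, ρ = 0.2 and correlation 0.3 the rate was 0.7%. Stronger clustering at that prevalence was not simulated with adjustment, so there the result rests on the formula.

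**Step 4: the same data with other standard errors.** Across the adjusted settings, including ones with almost no clustering, Poisson with robust variance rejected 4.4–6.4%, quasi-Poisson 2.7–5.7% and analysis of covariance 4.1–6.2%.

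**Step 5: the other named model.** Ordinary logistic regression on the individual days, ignoring that they come from the same person, understates the variance by the factor 1+13ρ at any prevalence. At ρ = 0.2 that is 3.6, giving 2[1 − Φ(1.96/√3.6)] = 30%; at ρ = 0.5 it is 7.5, giving 47%.

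**The case against.** The strongest objection is that the article never says model-based standard errors will be used. It names a model family, leaves room for judgement in applying it, and is a summary of a fuller protocol. A robust variance, a dispersion correction or an offset is the sort of detail an analysis plan may carry, and a binomial model is arguably within what the sentence allows. This stands in part. A reader might infer that the plan prescribes uncorrected Poisson regression; the text does not support that, so the point has to be conditional. What remains is that the named family carries a variance assumption that does not fit the endpoint defined elsewhere in the article, and the other named model does not help unless it too allows for clustering (step 5).

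Second, prevalence and correlation are assumed. The abstract describes urgency as part of the condition, so high prevalence is plausible, and there the test is near nominal or conservative. This stands: a general claim of badly inflated false positives is not supported.

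Third, the planned models are adjusted. Adjustment does lower the inflation, and at p = 0.7 with ρ = 0.2 none is left, but at p = 0.5 or with stronger clustering it persists.

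Fourth, multiple imputation partly answers the denominator issue. The article does not say whether single diary days or the whole count would be imputed, so that issue is secondary. Imputation changes neither the clustering nor the cap at 14.

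**Conclusion.** The point holds in conditional form. If days with urgency is analysed by Poisson regression with model-based standard errors, they will generally be wrong, and the direction cannot be told beforehand. For assumed within-person correlation of 0.2–0.5, an unadjusted nominal 5% test has a true size of about 14–31% at a mean of 7 days and 5–18% at 10 days. At a mean of 12 days or more, or where correlation lies below the break-even value in step 1, it is near nominal or conservative. With baseline adjustment the size is about 10–13% at p = 0.5 and ρ = 0.2.

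These sizes rest on a beta-binomial model and on prevalences and correlations that the document does not supply. It would go too far to conclude that this trial's urgency result will be falsely positive, or that the whole analysis is compromised: one of four clinical secondary endpoints is concerned, and the primary analysis of stool frequency by analysis of covariance is unaffected.

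**What to change.** State that days with urgency will be analysed as the proportion of diary days in weeks 11 and 12 with urgency, by binomial-family regression (fractional or quasi-binomial) with robust standard errors, adjusted for treatment arm, centre and baseline urgency proportion. This respects the cap at 14, and the robust standard errors are valid whichever way the variance departs from the model.

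At minimum, keep the Poisson model but specify a robust variance, with the log of completed diary days as offset where missing days are not imputed. Fix the choice before unblinding, because the variance estimator alone could decide whether the result is significant.

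The cost is one line of specification, with no change to data collection or sample size. Confidence intervals may become wider or narrower than under the model-based Poisson analysis, depending on how common and how clustered urgency proves to be.

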### Assessment of adverse events

This trial is using a drug, mesalazine, for which the side-effect profile is well established. Therefore the study specific definition of an adverse event was:

1) any study drug-related event as listed as a known side effects of mesalazine with the exception of diarrhoea and abdominal pain, which will only be recorded if these disease symptoms are exacerbated.

OR

2) any condition detected or diagnosed after the medicinal product has been administered and has a possible, probable or definite causal relationship with the study drug.

Due to the study specific definition the recording of adverse events and serious adverse event reporting began following the 1st dose of study treatment.

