#### Flexible Sigmoidoscopy and biopsies (Nottingham only

Patients will undergo an unsedated flexible sigmoidoscopy with biopsy of the sigmoid colon. Biopsies will be taken to investigate mast cells, mRNA for IL-1, TNF-α and protein levels, as well as for tryptase, serotonin and histamine release on incubation of mucosal biopsies.

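### Adverse events and SAEs are recorded only if linked to the study drug, so all-cause harm cannot be compared between arms and purely procedural complications fall outside the definition

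*Protocol article*

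**What the plan says.** The Assessment of adverse events section of the protocol article sets a study-specific definition with two limbs. The first is "any study drug-related event as listed as a known side effects of mesalazine with the exception of diarrhoea and abdominal pain"; those two symptoms are recorded only if they get worse. The second is a condition of any kind that comes to light after dosing and that "has a possible, probable or definite causal relationship with the study drug". The reason given is that mesalazine is a drug "for which the side-effect profile is well established". The same section says that "the recording of adverse events and serious adverse event reporting began following the 1st dose of study treatment". It gives no separate or wider rule for serious events.

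The Statistical analysis section states: "Assessment of safety followed the same principles as the assessment of efficacy". The safety set is "all randomised participants who receive at least one dose of the study drug". The Randomisation and blinding section says that participant, supervising doctor and study nurse do not know the allocation.

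On procedures, the section on flexible sigmoidoscopy, headed as applying to Nottingham only, says: "Patients will undergo an unsedated flexible sigmoidoscopy with biopsy of the sigmoid colon". Under Participant recruitment, some patients need a sigmoidoscopy with left-colon biopsy to establish eligibility.

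**The concern.** Randomisation and blinding allow harm to be judged by counting all events in each arm and comparing the counts, without anyone deciding case by case what the drug caused. This definition puts the case-by-case decision first. An event judged unrelated is never entered, in either arm, even if it later proves more common on mesalazine. The same applies to serious events.

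That fits poorly with a safety assessment run on the same principles as efficacy. It also relies on a side-effect profile that the article links to inflammatory bowel disease (Abstract). The earlier experience in IBS that the Background cites is open-label work and two small randomised trials. The harms most likely to be lost are those that nobody yet suspects.

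A second group of events is also affected. Some participants have a sigmoidoscopy with biopsy because of the trial. A complication put down to the procedure alone has no causal link to the drug and so is not an adverse event under this definition.

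**Working it through.** The plan states no figure on this point, so there is nothing to reproduce. The check has two parts.

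**1. Which events the rule captures**

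| Event | First limb | Second limb | Inside the recording window | Recorded |
|---|---|---|---|---|
| Known side effect, judged drug-related, after dosing | yes | yes | yes | yes |
| Unlisted condition, at least possibly drug-related, after dosing | no | yes | yes | yes |
| Any condition or SAE judged unrelated, after dosing | no | no | yes | no |
| Complication attributed only to sigmoidoscopy or biopsy, after dosing | no | no | yes | no |
| The same complication before the first dose | no | no | no | no |

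The first limb could be read more loosely, as taking in any listed side effect whatever its cause. Unlisted events would still depend on the second limb, so the conclusion would not change for them.

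On timing, the Mechanistic endpoint section places the mast cell count in weeks 11–12, so at least one trial biopsy comes after the first dose. A trial biopsy before dosing is plausible, because the Trial objectives include predicting response from mucosal markers. The text does not state one, and Figure 1 is not shown. Sigmoidoscopy for eligibility does come before dosing.

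**2. Effect on power (illustration)**

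Inputs:
- n = 108 / 2 = 54 per arm (Sample size section; completed participants, so the safety set may be somewhat larger).
- Two-sided significance level 5% (assumption).
- True event rates on placebo and mesalazine of 20% v 40%, or 10% v 30% (assumptions).
- A share q of events passes the causality judgement, equal in both arms because the judgement is blinded (assumption, ranged from 1 to 0.25).

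Recorded rates are p₁ = q × placebo rate and p₂ = q × mesalazine rate, with p̄ = (p₁ + p₂)/2. Then

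power = Φ{ [ (p₂ − p₁)√n − 1.96 √(2p̄(1 − p̄)) ] / √(p₁(1 − p₁) + p₂(1 − p₂)) }.

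For 20% v 40%, q = 1: (0.20 × 7.348 − 1.96 × 0.648) / 0.632 = 0.315, and Φ(0.315) = 0.62.

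For the same rates, q = 0.5: (0.10 × 7.348 − 1.96 × 0.505) / 0.500 = −0.51, and Φ(−0.51) = 0.31.

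| q | Risk difference (points) | Power, 20% v 40% (risk ratio 2.0) | Power, 10% v 30% (risk ratio 3.0) |
|---|---|---|---|
| 1 | 20 | 62% | 75% |
| 0.75 | 15 | 46% | 59% |
| 0.5 | 10 | 31% | 41% |
| 0.25 | 5 | 16% | 22% |

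The risk ratio is unchanged throughout. The recorded risk difference and the power both fall.

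**The case against.** The strongest reply is that a reader might infer from the definition that the arms cannot be compared on harm at all. The documents do not support that. The participant, doctor and nurse are blinded, the threshold is only a possible link, and the second limb takes in unlisted conditions. Nothing suggests that the filter works differently in the two arms, so suspected reactions remain a fair randomised comparison. This stands.

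A reader might also infer that starting at the first dose biases the comparison. It does not: the safety set is limited to participants who took a dose, so the window matches the set. The late start matters only for events before dosing.

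The procedural point is limited too. The trial biopsies are at one centre, the timing of any baseline biopsy is not stated, and a post-dose bleed judged possibly drug-related would be recorded. The article is a summary of protocol version 3.0, and the full document may deal with procedure complications elsewhere. These limits stand.

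Finally, the definition is a deliberate choice with a stated reason. That explains it but does not remove its effect. The article states the operative rule in full, so this is not a detail left to another document, and no analysis plan can compare events that were never collected.

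**Conclusion.** The point holds in a limited form. Under the stated rule, adverse events and SAEs judged unrelated to the drug are not recorded. All-cause totals therefore cannot be compared between arms, and the trial is less able to detect a harm that nobody suspects. Complications attributed only to a sigmoidoscopy or biopsy fall outside the definition at any time, and those before the first dose fall outside the window as well.

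The size depends on the share of events that blinded assessors would judge unrelated, which the documents do not give. Over the assumed range, power for a 20-point excess falls from 62–75% with full recording to 16–22% with a quarter recorded. This assumes that true drug effects and background events are filtered alike. If assessors dismissed background events more readily than true effects, the loss would be smaller. Even full recording would leave the trial with modest power for harm, so the gain is in completeness and in the chance of seeing an unexpected pattern. The change is worthwhile and cheap; the planned comparison of suspected reactions remains valid without it.

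**What to change.** Record all adverse events after the first dose in both arms, whatever their cause. Record SAEs and procedure complications from consent or from the first trial procedure. Hold attribution (drug, procedure, neither) as a separate field completed under blinding. Compare the arms on all post-dose events in the existing safety set, with drug-related events as a subset, and list pre-dose and procedural events separately.

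If that is too much, the minimum is to record all SAEs, all events leading to dose reduction or stopping, and all complications of sigmoidoscopy or biopsy.

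The cost is a protocol amendment, an attribution field in the eCRF and extra data entry over each participant's 14 weeks, with no new visits or procedures. The Trial status section gives recruitment from March 2011 to an expected end in May 2013. A change made during the trial would leave two recording rules, and events already passed over could not be reliably recovered, so events before and after the change must be reported separately. If the change can no longer be made, the report should state that its adverse events and SAEs are suspected drug reactions only and do not represent all-cause harm.
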